#### Sample Size Determination

Effect sizes for rTMS on cognition in the PD literature are variable, with a range of 0.04 [51] to 0.36 [14]. However, there are several limitations to these studies that lead us to believe that the effect size will be larger in the population with PD-MCI. First, given that the existing literature has studied patients with PD-N, it is reasonable to expect that cognitive effects in these studies may have been limited by a ceiling effect such that cognitive function could not have improved any further [8]. In addition, not all the existing PD studies have used neuronavigation, so variability was likely increased in terms of the actual site being stimulated [52]. Such treatment variability can increase variability in cognitive outcome measures and, thus, lower the effect size [53]. Finally, all existing PD literature examining cognitive effects has used 100% the RMT or less. As people age, cortical atrophy occurs, leading to increased scalp-to-cortex distance. This atrophy occurs more in the prefrontal regions compared to the motor cortex [54]. If this is not compensated for, it can weaken rTMS stimulation intensity. Thus, effects observed using relatively lower stimulation intensity (80%-100%) likely underestimate the benefits of rTMS for executive function in PD studies. One way to compensate for this is to increase the RMT to above 100%.

The limitations of existing data indicate that rTMS effect sizes on cognition in Alzheimer disease are likely more accurate for sample size determination in this study. Similar to PD, patients with Alzheimer disease experience cognitive deficits and have overlapping brain regions undergoing neurodegeneration. A meta-analysis [55] estimated a moderate effect size of 0.48 in terms of the benefits of rTMS (with many of the included studies targeting the DLPFC) for cognition among older patients with cognitive impairment related to Alzheimer disease.

Taking all this into consideration, as well as the fact that this is a small-scale trial, the effect size of 0.48 found in the aforementioned meta-analysis [55] was estimated for this RCT. The sample size was determined using a 2-level mixed-effects longitudinal model with random participant intercept and random participant slope. The end point effect size was fixed at 0.48, which is considered moderate. The participant intercept and slope variances were fixed at 2.3 and 0.3, respectively. In addition, the error variance was fixed at 2.0, which should be considered moderate. Using this combination of parameters, we determined that a sample size of 71 per group (active and sham) considering an attrition rate of 10% will be needed to achieve 80% power while maintaining the type 1 error rate at 5%. The RMASS software was used for this power analysis [56]. Hence, a total of 156 participants will be recruited for this proposed study.

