### Objectives

The research objective is to examine the therapeutic effects of rTMS on cognitive function in veterans with PD-MCI. The central hypothesis is that rTMS will safely improve cognitive function in PD-MCI.

There are 2 aims of the study. Aim 1 is to determine the safety and feasibility of rTMS treatment. The hypothesis is that 10 high-frequency rTMS sessions will be (1) safe, as evidenced by the lack of difference in the number of research-related adverse events experienced by the active rTMS group compared to the sham rTMS group; and (2) feasible, as indicated by participant protocol completion rates.

Aim 2 is to determine the behavioral effects of rTMS treatment. A battery of neuropsychological tests will be administered at baseline, end point (after the 10th rTMS session), and the 1-month follow-up. The hypothesis is that active rTMS, compared to sham rTMS, will enhance cognitive test performance after rTMS completion and at the 1-month follow-up. The primary outcome will be change in executive function (ie, end point minus baseline) as measured using the National Institutes of Health–sponsored Executive Abilities: Measures and Instruments for Neurobehavioral Evaluation and Research (NIH-EXAMINER) Executive Composite score.

To address the study objectives, a prospective parallel-group RCT will be conducted. A convenience sample of veterans (N=66) who have been screened and diagnosed with PD-MCI will be randomly assigned to 1 of 2 groups: active rTMS or sham rTMS to the left DLPFC.

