For neuropsychological outcomes, all data will be analyzed using a 2-level longitudinal mixed-effects model with random participant effects to incorporate correlation of measurements nested within the same participant. The model will also include covariates such as medication dose and anxiety and depression levels. Parameters will be estimated using measurements from all 3 time points (ie, baseline, end point, and follow-up). The group-by-time interaction parameter will be used to examine the difference in the trends of the active rTMS group compared to the sham rTMS group. The significance of this parameter will indicate whether treatment is efficacious in terms of executive function over time when adjusted for the identified covariates. To assess the immediate effects of rTMS, one contrast using means of test scores at baseline and end point from the experimental group will be obtained, and the other contrast will be obtained from those same types of means for the control group. These 2 contrasts will then be tested using a 2-tailed *t* test to compare the change scores of the 2 groups. To assess sustainability of the rTMS effects, contrasts using means of test scores at end point and follow-up will be obtained for each group, and the contrast will then be compared using a *t* test. Estimates of variance components from mixed-model analysis will be used to calculate test statistics. To account for the many-to-many comparisons of secondary outcomes, we will use a multivariate mixed-effects model with the aforementioned covariates. For every secondary outcome component, there will be fixed as well as random components. The random component will address the within-subject correlation and the heterogeneity between multiple outcomes. Every component will have its own trend, which means that the recovery curve may be outcome specific. The group-by-time interaction parameter of each secondary outcome will be tested to examine whether cognitive function in the active rTMS group is different from that in the sham rTMS group. The false discovery rate will be addressed using Benjamini and Hochberg [57] procedures, with a false discovery rate level of 0.05. Data analysis will be performed using the SAS PROC MIXED statement (version 9.3; SAS Institute). This modeling process will be reported for each outcome of interest for the safety and neuropsychological assessments. Every effort will be made to avoid missing data; we will try to understand the missingness pattern and why and how the missingness occurred. No missing value imputation technique will be used if Little test supports that data are missing completely at random. Otherwise, proper missing data imputation techniques (eg, imputation with mean, nearest neighbor, or last observation carried forward) will be used.

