## Results

This project was funded in June 2019, with additional funding secured in April 2024. A no-cost extension was recently received. As of April 2025, a total of 18 veterans with PD-MCI have completed the RCT phase. Data collection is ongoing and will be completed by March 2027. We expect the results of this study to be available by March 2028.

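### The protocol randomises 66 but needs 71 per group and recruits 156; these figures cannot be reconciled, and at 66 the power for the stated effect is about 45–50%, not 80%

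*Protocol article*

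**What the plan says.** The Objectives section fixes the number to be randomised: "A convenience sample of veterans (N=66) who have been screened and diagnosed with PD-MCI will be randomly assigned to 1 of 2 groups". With equal allocation that is 33 per group.

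The Sample Size Determination section gives different figures. It assumes an end-point effect size of 0.48 and a two-level mixed model with intercept variance 2.3, slope variance 0.3 and error variance 2.0. It states that "a sample size of 71 per group (active and sham) considering an attrition rate of 10% will be needed to achieve 80% power", with type 1 error at 5%. The next sentence but one is: "Hence, a total of 156 participants will be recruited for this proposed study".

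The printed numbers are therefore 66, 71 per group and 156. The total of 142 is 2 × 71 and does not appear in the text.

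**The concern.** The randomised total determines the power, the precision and the point at which the trial counts as complete. Here it takes values that differ by more than a factor of two, and the text does not say which one governs.

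There are two separate problems:

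- **66 against 71 per group.** Randomising 66 supplies less than half of the stated per-arm requirement.
- **71 per group against 156.** The second figure is introduced as a consequence of the first, yet doubling 71 gives 142.

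The harm lies in how the result is read. If 66 are randomised and readers hold the result against the only power figure in the protocol, a non-significant primary result would look like fair evidence against an effect of 0.48. In fact the trial would miss that effect about half the time.

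**Working it through.** **Inputs.** From Sample Size Determination: effect size 0.48, variances 2.3 / 0.3 / 2.0, power 80%, type 1 error 5%, attrition 10%, 71 per group, 156 in total. From Objectives: 66 randomised. From the statistical methods section: a 2-tailed test of the change-score contrast and three measurement occasions. Assumed because the text does not give them: 1:1 allocation, zero intercept–slope covariance, time coded 0, 1, 2, and 0.48 expressed in units of the outcome SD at the later visit.

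**1. Reproducing 71 per group**

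*Mixed-model reading, baseline to end point:*
- Variance of change = 0.3 + 2 × 2.0 = 4.3
- SD at end point = √(2.3 + 0.3 + 2.0) = 2.145
- Difference = 0.48 × 2.145 = 1.03
- n per group = 2 × (1.96 + 0.842)² × 4.3 / 1.03² = 63.7, so 64
- With 10% attrition: 63.7 / 0.9 = 70.8, so 71

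The three-occasion version gives 64.4 per group without attrition. Modelling 10% total dropout directly gives 69.0–70.3. On this reading 71 already includes attrition.

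*Plain two-group reading:*
- n per group = 2 × (1.96 + 0.842)² / 0.48² = 68.1, so 69; the t test needs 70

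On this reading 71 is close to the number before attrition.

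The stated figure is thus reproduced to within 2 in two ways, with opposite implications for attrition. Other scalings of 0.48 do not settle it. The change-score SD gives about 68 before attrition and 73–80 after; the baseline SD gives about 82 before and 88–96 after.

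**2. The step to 156**

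| Route | Total |
|---|---|
| 2 × 71, attrition already included | 142 |
| 142 × 1.1 | 156.2 |
| 70 completers per group / 0.9 = 77.8, so 78 per group | 156 |
| 71 completers per group / 0.9 = 78.9, so 79 per group | 158 |

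The second row is a second allowance if 71 already includes attrition. The third row is a single allowance.

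**3. Power if 66 are randomised** (effect 0.48, two-sided 5%)

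Normal approximation: Φ(0.48 × √(n/2) − 1.96). Mixed-model end-point contrast: Φ(1.03 / √(8.6/n) − 1.96).

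| Method | 33 per group, all retained | 10% attrition (29.7 per group) |
|---|---|---|
| t test | 0.484 | 0.444 |
| Normal approximation | 0.496 | 0.456 |
| Mixed model | 0.518–0.523 | about 0.48–0.49 |

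None of the alternative scalings or time codings tried raised power at 33 per group above about 0.52. A one-sided 5% test, which the protocol does not propose, would give only about 0.62 with full retention.

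**4. Effect detectable with 80% power if 66 are randomised**

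- Mixed-model contrast: 2.802 × √(8.6/33) / 2.145 = 0.67; with 30 per group, 0.70
- t test: 0.70 with 33 per group; 0.74 with 30 per group

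The range is about 0.67–0.74, against the planned 0.48.

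**The case against.** **Recruited and randomised may be different counts.** Consent comes before cognitive screening in the study flow, so 156 could be those who consent and 66 those who go on to randomisation. This does not help: 71 is the stated need in each treatment arm, and 66 randomised provides 33.

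**80% power is never claimed for 66.** This is correct. The protocol attaches 80% to 71 per group, and a reader who infers that it claims 80% at 66 goes beyond the text. The power shortfall is conditional on 66 being the real target. The inconsistency is not conditional.

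**Attrition counted twice.** A reader might take this as established, since the wording says attrition is already considered and the stated variances can give 64 / 0.9 ≈ 71. It is not proven. That derivation relies on time coding, covariance and effect scaling that the protocol does not give, and about 70 completers per group with one allowance also leads to exactly 156. For the same reason the documents do not support an instruction to replace 156 with 142.

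**The trial already presents itself as small.** It is called a pilot in the Data Monitoring section and small-scale in the sample size section, and the Abstract speaks of preliminary effects. That softens the concern in part, but the Objectives still state efficacy as a hypothesis to be tested, and the 80% figure carries no qualification.

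**Accrual.** From "As of April 2025, a total of 18 veterans with PD-MCI have completed the RCT phase" a reader might forecast the final sample. The documents give a funding date but no recruitment start, and do not count participants in progress, so no reliable rate can be derived.

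**Conclusion.** The concern holds in this form. A randomised total of 66 contradicts a requirement of 71 per group and a recruitment total of 156, and nothing in the article reconciles them. Separately, the sentence leading to 156 is inconsistent as written, whichever explanation is true: either the total or the attrition phrase is wrong.

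If 66 governs, power for an effect of 0.48 is about 0.48–0.52 with full retention and 0.44–0.49 with 10% attrition, and 80% power is reached only at about 0.7 SD. This assumes equal allocation and a two-sided 5% test. The t-test figures need none of the unstated mixed-model settings, so the power conclusion does not hinge on them. Whether 71 is before or after attrition does hinge on them, and only the authors can answer it.

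**What to change.** 1. State one number to be randomised and use it in both Objectives and Sample Size Determination. If a larger number is to be consented to allow for screening loss, give it separately and label it.
2. Say whether 71 per group is before or after attrition. The total is 142 if after and about 156–158 if before, depending on rounding. Give the time coding, the intercept–slope covariance and the SD that scales 0.48, so that the figure can be checked.
3. If 66 is the operative number, replace the 80% statement with about 45–50% power for an effect of 0.48 and 80% power for an effect of about 0.7. Describe the efficacy analysis as preliminary and report it as an estimate with a 95% confidence interval, so that a non-significant result is not read as absence of effect.

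The cost is a change of wording. If 66 stands, the stated power becomes less favourable.

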#### Recruitment

Military veteran participants will be recruited through VA national databases, clinician referrals, and flyers placed in the 2 participating VA hospitals.

### Assignment of Interventions

Participants will be randomized to either the active or sham rTMS. The sequence will be produced by the study biostatistician using an online random number generator. There will be no stratification. An unblinded study team member will assign the participant number series codes from the MagVenture study master edition. These participant codes correspond to randomized treatment numbers that are entered into the MagVenture MagProX100 stimulator before each treatment session.

Participants and study team members administering and scoring outcome measures, as well as the study biostatistician, will be blinded to group assignment. Researchers blinded to treatment group will administer outcome measurements. The effectiveness of blinding will be evaluated using data collected from end point questionnaires that assess perception of the intervention.

Unblinding will occur after participants have completed the study.

### Data Collection, Management, and Analysis

#### Data Collection Methods

Figure 1 [25,50] illustrates plans for assessment and collection of outcomes during screening, baseline, end point, and follow-up visits.

#### Data Management Methods: Statistical Methods

For safety outcomes, the Poisson distribution for the number of research-related adverse events will be fitted for each treatment group. Negative binomial distributions will be used in case overdispersion is present. The mean parameters (λ) of these 2 distributions will be tested to see whether any difference in the average number of adverse events in each treatment group exists. Lack of significance will suggest that active rTMS is as safe as sham rTMS in terms of adverse events. To further compare the trend in adverse events between the 2 groups, we will use a 3-level mixed-effects Poisson regression model, and the group-by-time interaction parameter will be tested to examine whether active rTMS has more adverse events than sham rTMS over time.

For neuropsychological outcomes, all data will be analyzed using a 2-level longitudinal mixed-effects model with random participant effects to incorporate correlation of measurements nested within the same participant. The model will also include covariates such as medication dose and anxiety and depression levels. Parameters will be estimated using measurements from all 3 time points (ie, baseline, end point, and follow-up). The group-by-time interaction parameter will be used to examine the difference in the trends of the active rTMS group compared to the sham rTMS group. The significance of this parameter will indicate whether treatment is efficacious in terms of executive function over time when adjusted for the identified covariates. To assess the immediate effects of rTMS, one contrast using means of test scores at baseline and end point from the experimental group will be obtained, and the other contrast will be obtained from those same types of means for the control group. These 2 contrasts will then be tested using a 2-tailed *t* test to compare the change scores of the 2 groups. To assess sustainability of the rTMS effects, contrasts using means of test scores at end point and follow-up will be obtained for each group, and the contrast will then be compared using a *t* test. Estimates of variance components from mixed-model analysis will be used to calculate test statistics. To account for the many-to-many comparisons of secondary outcomes, we will use a multivariate mixed-effects model with the aforementioned covariates. For every secondary outcome component, there will be fixed as well as random components. The random component will address the within-subject correlation and the heterogeneity between multiple outcomes. Every component will have its own trend, which means that the recovery curve may be outcome specific. The group-by-time interaction parameter of each secondary outcome will be tested to examine whether cognitive function in the active rTMS group is different from that in the sham rTMS group. The false discovery rate will be addressed using Benjamini and Hochberg [57] procedures, with a false discovery rate level of 0.05. Data analysis will be performed using the SAS PROC MIXED statement (version 9.3; SAS Institute). This modeling process will be reported for each outcome of interest for the safety and neuropsychological assessments. Every effort will be made to avoid missing data; we will try to understand the missingness pattern and why and how the missingness occurred. No missing value imputation technique will be used if Little test supports that data are missing completely at random. Otherwise, proper missing data imputation techniques (eg, imputation with mean, nearest neighbor, or last observation carried forward) will be used.

Potential moderators of the effects of rTMS will be explored through Pearson correlations and regression analyses. Factors include, for example, age at study enrollment, age at PD onset, disease duration, MoCA score, levodopa equivalent dose, and change in mood (eg, depression, anxiety, and apathy). Blinding success will be reported alongside the primary results.

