**Results:**

Safety will be assessed using the number of research-related adverse events experienced by the active rTMS group compared to the sham rTMS group. Feasibility will be assessed using protocol completion rates. To examine preliminary effects of rTMS, participants will complete a standardized neurocognitive battery assessment at baseline, end point, and 1-month follow-up. The primary study outcome is the change in score from baseline to end point on the National Institutes of Health–sponsored Executive Abilities: Measures and Instruments for Neurobehavioral Evaluation and Research Executive Composite score. This project was funded in June 2019, with additional funding secured in April 2024. As of April 2025, a total of 18 veterans with PD-MCI have completed the randomized controlled trial phase. Data collection is ongoing and will be completed by March 2027. We expect the results of this study to be available by March 2028.

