There is considerable evidence that rTMS performed in compliance with the recommended safety guidelines [19-21] is reasonably safe with mild side effects. The most serious risk of rTMS is seizures; however, the risk of seizure in healthy persons is exceedingly low [22]. A safety review indicates no reported rTMS-induced seizures in the PD population and that the more common safety issues related to rTMS in PD are similar to those in the non-PD population [23]. The most common side effects include a mild transient headache, scalp pain at the stimulation site, neck pain, tooth pain, transient changes in audition, and syncope. While rTMS is considered a safe procedure when provided within safety guidelines, it is important to remember that it is an experimental treatment in PD without Food and Drug Administration (FDA) clearance. Thus, there may be unknown risks. Safety is of the highest priority; thus, it is critical that investigators measure and report on the presence or absence of adverse events [19]—this will help address existing gaps in the PD rTMS safety literature.

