#### Harms: Safety Monitoring

All study procedures and parameters are in accordance with the current safety and application guidelines for rTMS [19,21]. Treatment will be delivered by personnel trained in the administration of rTMS. An rTMS data safety monitoring sheet (DSMS), adverse event tracking log, medication log, and sleep log for each participant will be kept to monitor session attendance and any side effects or adverse events according to prespecified criteria. The Columbia-Suicide Severity Rating Scale will also be administered at the baseline, end point, and follow-up assessments.

The DSMS contains a customized severity indicator scale with before-and-after variables, including rates of change from baseline in vital signs (temperature, blood pressure, heart rate, and oxygen saturation levels), fatigue, tinnitus, sleep, dizziness, nausea, vomiting, confusion, seizure, syncope (fainting), headache, neck pain, skin integrity of the scalp, and movement. PD-related motor assessments, including speech, facial expression, finger taps, rapid alternating movement of the hands, tremor at rest, leg agility, ability to rise from a chair, gait, and body bradykinesia and hypokinesia, will also be conducted before and after each rTMS session and compared to baseline.

An adverse event tracking log will also be developed for this project for further safety monitoring. All serious and nonserious adverse events will be tracked on this log.

Sleep disruption and deprivation is associated with a lower seizure threshold, which may put the participant at a heightened seizure risk when receiving rTMS. Therefore, the sleep log asks the participants to record total hours of sleep at night and total minutes of nap time during the day. After the baseline assessment, a study team member will provide a sleep packet (collection of blank sleep logs) for the participants. The participants will then receive instructions on how to use the log. Data collected before the first rTMS session will be averaged, and variance will be documented and used as the baseline for the DSMS. At least 3 days of “total hours of sleep” will be required for the participant to complete the first session of rTMS. During the study period, self-reported sleep based on the sleep log will be checked before the intervention is administered for a given day.

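### The safety count is limited to research-related adverse events, but the conclusion drawn from it is worded for adverse events in general, and no arm comparison of the full event log is clearly described

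*Protocol article*

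**What the plan says.** Under Data Management Methods: Statistical Methods, the protocol article names the endpoint of the main safety model: "the Poisson distribution for the number of research-related adverse events will be fitted for each treatment group". It then describes the test as asking "whether any difference in the average number of adverse events in each treatment group exists", and it draws this conclusion from a null result: "Lack of significance will suggest that active rTMS is as safe as sham rTMS in terms of adverse events". A three-level Poisson model follows, in which "the group-by-time interaction parameter will be tested to examine whether active rTMS has more adverse events than sham rTMS over time". Neither the conclusion nor the trend model repeats the relatedness limit.

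Elsewhere the limit is explicit. The Objectives define rTMS as "safe, as evidenced by the lack of difference in the number of research-related adverse events experienced by the active rTMS group", the abstract says "Safety will be assessed using the number of research-related adverse events experienced by the active rTMS group compared to the sham rTMS group", and the Discussion repeats the hypothesis in the same terms.

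Collection is wider than analysis. Under Harms: Safety Monitoring the article says of the adverse event log: "All serious and nonserious adverse events will be tracked on this log". The Background describes rTMS in Parkinson disease as experimental and adds: "Thus, there may be unknown risks".

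**The concern.** A count restricted to events that someone has already linked to the research is poorly suited to detecting risks that nobody yet expects. Several signs on the monitoring sheet, such as gait, tremor, slowness of movement and confusion, can also belong to the disease, so attribution may be difficult in this population. In a randomized sham-controlled trial the sham arm supplies the background rate, and a comparison of all events needs no attribution.

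The direction of the error matters because the plan reads non-significance as reassurance. Each true harm classed as unrelated leaves the count and moves the result toward a finding of safety. A reader of the final report could also take a statement about adverse events to cover events that were never in the test.

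**Working it through.** **Event definitions, side by side**

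| Place in the article | Events meant |
|---|---|
| Abstract, Objectives, Discussion | research-related |
| Statistical Methods, main count model | research-related |
| Statistical Methods, quantity compared and conclusion | adverse events, unqualified |
| Statistical Methods, trend model | adverse events, unqualified |
| Safety Monitoring, log | all, serious and nonserious |

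The hypothesis and the main model agree with each other. The mismatch lies in how the Statistical Methods section words the result. The full log is collected but is not assigned a comparison, unless the trend model is meant to be one.

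**Size**

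The article gives no adverse event rate, margin or power for safety, so there is no stated figure to reproduce. What follows is an illustration, and every rate in it is an assumption.

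Inputs:
- Participants per arm, n: 33 (half of the 66 in the Objectives), 71 (the per-group figure under Sample Size Determination) and 78 (half of the 156 there), with equal allocation assumed. All three are shown because the article gives all three.
- Two-sided alpha 5%. The article states this for efficacy; it is assumed here for safety.
- Related events in the sham arm: 0.5 per participant (assumed).
- True excess in the active arm: 0.5 per participant (assumed), of which a share m is judged unrelated.
- Unrelated background in both arms: b = 0.25, 0.5 or 1.0 per participant (assumed).

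Formulas, for a Wald test of the log ratio of two Poisson means:
- SE = sqrt(1/(n·λ1) + 1/(n·λ0)), z = ln(λ1/λ0)/SE
- power = Φ(z − 1.96) + Φ(−z − 1.96)
- related-only: λ1 = 0.5 + 0.5(1 − m), λ0 = 0.5
- all events: λ1 = 1.0 + b, λ0 = 0.5 + b

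Worked for n = 33:
- Related-only, m = 0: SE = sqrt(1/33 + 1/16.5) = 0.3015, z = 0.6931/0.3015 = 2.30, power 63.3%.
- Related-only, m = 0.5: SE = sqrt(1/24.75 + 1/16.5) = 0.3178, z = 0.4055/0.3178 = 1.28, power 24.8%.
- All events, b = 0.5: SE = sqrt(1/49.5 + 1/33) = 0.2247, z = 0.4055/0.2247 = 1.80, power 43.8%.

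| n per arm | Related-only, m = 0 | m = 25% | m = 50% | m = 100% | All events, b = 0.25 | b = 0.5 | b = 1.0 |
|---|---|---|---|---|---|---|---|
| 33 | 63.3% | 44.2% | 24.8% | 5.0% | 52.0% | 43.8% | 33.4% |
| 71 | 92.1% | 75.8% | 46.5% | 5.0% | 83.8% | 75.4% | 61.2% |
| 78 | 94.2% | 79.6% | 50.1% | 5.0% | 87.1% | 79.2% | 65.3% |

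With a smaller excess of 0.25 and n = 33, the related-only figures are 24.8%, 16.6%, 10.4% and 5.0%, and the all-event figures are 19.1%, 15.9% and 12.5%.

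Two things follow. The related-only test loses power as true harms are judged unrelated, and falls to the error rate if all of them are. The all-event test is unaffected by attribution but pays for background events. At b = 0.5 it overtakes the related-only test only once m slightly exceeds 25%. At b = 1.0 the crossover lies between 25% and 50%. Neither count is better in every case.

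**The case against.** The strongest reply is that the article is open about its endpoint. Three other places limit the safety hypothesis to research-related events, so the unqualified wording in Statistical Methods may be shorthand for the endpoint just named. This mostly stands: a reader might infer that the trial claims safety for all adverse events throughout, and the article does not support that. The conclusion sentence still lacks the limit, and the report's wording may follow it.

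A reader might also infer that harms attributed to the disease disappear from the trial. They do not. All events are logged. Depression, anxiety and apathy scales are secondary outcomes, each with a group-by-time test that needs no attribution. Motor signs are checked before and after every session, and suicidality is rated at three visits. This stands as partial cover, although no arm comparison of the motor checks is described.

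A third tempting reading is that attribution biases the arm comparison. The trial is described as double-blind, and noise masking extends to treatment providers. If relatedness is judged blind, misclassification dilutes a true difference and does not create a false one. The article does not say who judges relatedness, but that is a detail a condensed article may leave to the full protocol.

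Finally, the trend model might already count all events, and a supplementary all-event table might sit in an analysis plan that is not shown. Either is possible. What remains is the stated choice of events for the main test and a conclusion worded more widely than that choice.

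**Conclusion.** The point holds in limited form. The only safety model with a clearly named endpoint counts research-related events, its conclusion is worded for adverse events at large, and the events in the trend model are unspecified. A true rTMS harm judged unrelated would be absent from the count that supports the safety statement.

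Provided attribution is blind, the consequence is reduced sensitivity to unexpected harms, in a plan that treats a null result as reassuring. The size cannot be derived from the document: the power figures rest entirely on assumed rates, and any particular misattribution rate would be a guess. That motor or other events would in fact be attributed to Parkinson disease is an inference, not something the article says. This is a low-cost improvement and not a flaw that invalidates the safety analysis. Whether non-significance can show equal safety at all, and which sample size applies, are separate questions and carry no weight here.

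**What to change.** - Keep the research-related count as planned.
- Fit the same Poisson or negative binomial model to all logged adverse events regardless of attribution, and compare serious events by arm.
- Report these results side by side.
- State which events the three-level trend model counts.
- Word the safety statement for the events actually analysed: research-related events if it rests on that count alone.

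The cost is an additional run of a model already planned, a serious-event comparison and a few words of text, using data already on the log. The downside is that background events make the all-event comparison noisier. In the illustration with 33 per arm, its power is 33.4% to 52.0%, against 63.3% for the related count with perfect attribution. For that reason it should stand beside the related count and not replace it.
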